**Fig. 3 Fig3:**
[figure not shown]
Cascade training model and assessments of trainers and providers

#### Training of frontline primary care providers

Subsequent to the ToT, the trained trainers will conduct training workshops with the end-users of mhGAP-IG. This training will utilize the training materials developed by the Master Trainers and will be supervised by the Master Trainers. We plan for each training workshop to be facilitated by at least two of the trained Trainers. Each 2-day workshop will be attended by no more than 20 participants to ensure effective and interactive training. Participants will be tested pre- and post-training on knowledge and attitude. They will also provide structured ratings on the content and delivery of the training. At the end of each training workshop, the Master Trainer will have a de-briefing session with the Trainers during which a review of the workshop will be conducted and lessons learnt noted.

#### Use of a screening instrument

We will explore the impact of the incorporation of a short screening tool for depression into the routine clinical assessment of women presenting for antenatal care. After the training of the providers in the use of mhGAP-IG for the detection and treatment of perinatal depression, participating clinics will be divided into two groups. In one group of randomly selected clinics, providers will use the 2-item Patient Health Questionnaire (PHQ-2) to routinely screen consecutive women attending maternal clinics to determine need for further assessment for depression. Providers in the second group of clinics will not be using a screening tool before assessing the antenatal women for depression.

#### Assessing knowledge retention

Approximately 6 months after the initial training, 40 of the trained PHCW, randomly selected, will receive another test to determine the level of knowledge retention, the level of drift in the acquired skills and factors that are related to retention or drift. Such factors may be the characteristics of the providers, including their level of clinical experience, post-training performance, age, or level of clinical support.

#### Refresher training

Approximately 6 months after the initial training of frontline primary care providers, a refresher training essentially like the initial one will be provided for the PHCW in the PHQ-2-using clinics. Participants at this training will also be tested pre and post training.

#### Supportive supervision

The frontline providers in all the clinics will have structured fortnightly supportive supervision conducted by the trainers. A structured checklist will be designed to cover clinic organization and service delivery activities geared towards identifying and providing care for perinatal depression, on which the supervisors can score each clinic on a Likert scale. The supervisors will also provide technical and other assistance to the frontline providers as needed.

## Methods phase four

### Participants

Consecutive women making their first antenatal visit will be screened for depression with the EPDS after their consultation with the primary care providers (Fig. 2). Women who screen positive will be invited to participate in the study. At an estimated prevalence of at least 10% and about 5% refusals, we expect to screen about 3500 women to recruit 334 women with scores at or above the cut-off level (see section on sample size determination) and consenting to participate in the study. Women who screen positive, irrespective of whether they have been identified as depressed by the PHCW, and who provide informed consent to participate will constitute Cohort Two for the study. Those who screen positive but have not been identified by the primary care workers will be advised to see the providers again and notify them of their depression status. This will be particularly so for those who score 18 or more or have suicidal ideation on the EPDS and are therefore judged to have severe depression as well as those who endorse the item on suicidality on the EPDS. This is to ensure that they get timely treatment. The providers are also required to consult with the project psychiatrist for the management of patients with serious suicidal risk.

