**Method:**

This project is a hybrid implementation-effectiveness study guided by the Replicating Effective Programmes Framework. It will be conducted in four overlapping phases in maternal care clinics (MCC) in 11 local government areas in and around Ibadan metropolis, Nigeria. In Phase I, engagement meetings with relevant stake holders will be held. In phase II, the organizational and clinical profiles of MCC to deliver chronic depression care will be assessed, using interviews and a standardized assessment tool administered to staff and managers of the clinics. To ascertain the current level of care, 167 consecutive women presenting for antenatal care for the first time and who screened positive for depression will be recruited and followed up till 12 months post-partum. In phase III, we will design and implement a cascade training programme for PHCW, to equip them to identify and treat perinatal depression. In phase IV, a second cohort of 334 antenatal women will be recruited and followed up as in Phase I, to ascertain post-training level of care. The primary implementation outcome is change in the identification and treatment of perinatal depression by the PHCW while the primary effectiveness outcome is recovery from depression among the women at 6 months post-partum. A range of mixed-method approaches will be used to explore secondary implementation outcomes, including fidelity and acceptability. Secondary effectiveness outcomes are measures of disability and of infant outcomes.

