### Procedure

Consecutively registered women presenting for antenatal care will be screened with the EPDS after being attended to by the PHCW (Fig. 2 and SPIRIT guideline). All those who screen positive for depression, irrespective of whether they have been identified as having depression by the PHCW or not, and consent to participate in the study will constitute Cohort One. At an estimated prevalence of at least 10% and about 5% refusals, we expect to screen about 1800 women to recruit 167 women with scores at or above the cut-off level and consenting to participate in the study (see below for sample size estimation). This cohort will enable us determine how many of those who screen positive are identified by the PHCW and what treatment is offered to them. Even though this cohort is to document current treatment practices in these clinics for women with depression, any woman considered to be at high risk will be referred for treatment. This will include women with severe depression as indicated by an EPDS score of 18 or greater and those with suicidal ideation as indicated by a score of 3 or more on the tenth item of the EPDS. Severely depressed or suicidal subjects will be tracked to see if they took up referral and additional care, as part of process evaluation. Women who are too ill to cope with the interview or require urgent medical attention will be excluded from recruitment.

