### Interventions

The interventions will be based on treatment specifications in the WHO Mental Health Gap Action Programme Intervention Guide (mhGAP-IG) as adapted for the health system of Nigeria [27]. The mhGAP-IG depression module provides detailed guideline for the management of moderate to severe depression with special consideration for pregnant or breastfeeding women. The mhGAP-IG emphasizes the use of psychosocial interventions for depression in pregnant and breast-feeding women with the lowest effective dose of an antidepressant being used when there is no response to psychosocial treatments. In line with this, interventions for perinatal depression in this study will include psychoeducation, addressing current psychosocial stressors and reactivating social networks.

Psychoeducation will be offered to every woman enrolled into the study as well as to their family members as appropriate. Psychoeducation involves an explanation of the diagnosis to the patient in simple language using local expressions while avoiding the labelling of ‘mental illness/disorder’. The patient is helped to understand that the symptoms being experienced are not as a result of laziness or supernatural forces but an ailment that is common and amenable to treatment. Addressing current psychosocial stressors entails offering the patient an opportunity to talk about current psychosocial problems and, to the extent possible, the health worker addressing pertinent social issues and assisting the patient to solve the problems with the support of available community resources. In reactivating social networks, the patient is encouraged to re-initiate prior social activities that have been neglected on account of the illness.

The health worker is expected to follow up the patient regularly. However, the choice of the number and frequency of the visits will be at the discretion of the attending health care provider. Low dose medications will be indicated for women who do not improve with the psychosocial treatments. Medication will only be given after consultation with the primary care physician.

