## Outcome measures

### Primary outcomes

The primary implementation outcome is change in the identification of perinatal depression between the two cohorts by the providers. The primary effectiveness outcome is difference in remission rates from depression at 6 months between the two patient cohorts. Remission is defined as an EPDS score of 5 or less at 6 months post-partum.

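### The 6-month remission contrast mixes provider training with the study's own EPDS case-finding, because unidentified women below the high-risk criteria are advised to return to the provider only in Cohort Two

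*Protocol article*

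**What the plan says.** All of this is in the Protocol article.

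- **Cohort One** (Methods phase two, Procedure). Women are screened with the EPDS after their consultation and enrolled whether or not the provider recognised depression. The stated purpose is that "this cohort is to document current treatment practices in these clinics for women with depression". The only stated action on the EPDS result is that "any woman considered to be at high risk will be referred for treatment". On who counts as high risk: "This will include women with severe depression as indicated by an EPDS score of 18 or greater", together with women scoring 3 or more on item 10.
- **Cohort Two** (Methods phase four, Participants). Screening again follows the consultation. "Those who screen positive but have not been identified by the primary care workers will be advised to see the providers again" and to notify them of their depression status. The next sentence adds emphasis but does not narrow the rule: "This will be particularly so for those who score 18 or more or have suicidal ideation on the EPDS". The stated aim is timely treatment.
- **Care tied to enrolment.** Table 1 enters provider mhGAP treatment at enrolment for Cohort Two and has no such entry for Cohort One. Interventions, within the phase four text, states: "Psychoeducation will be offered to every woman enrolled into the study".
- **Outcomes.** Under Primary outcomes: "The primary implementation outcome is change in the identification of perinatal depression between the two cohorts by the providers". In the Abstract: "The primary implementation outcome is change in the identification and treatment of perinatal depression by the PHCW". The primary effectiveness outcome is the difference between cohorts in remission at 6 months.

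**The concern.** The cohorts are meant to differ in whether providers had been trained. They also differ in what the study does once its own EPDS is positive. An unidentified woman below the high-risk criteria is left to usual practice in Cohort One, but in Cohort Two she is advised to go back and disclose her depression. Study instruments says that research assistants administer this EPDS, so the extra case-finding comes from the study and not from the clinic.

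Design and Outcome assessments read the cohort difference as the effectiveness of care delivered after training. Part of any remission gain could instead depend on a step that would be absent at scale-up, where no research EPDS exists. A treatment-received outcome, which the Abstract places within the primary implementation outcome, is exposed to the same step. Blinding and protection against sources of bias deals only with the PHQ-2 comparison. The limitations in the Discussion name outside events such as other in-service training, not this difference in procedure.

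**Working it through.** **1. The plan's own figure.** Sample size gives 167 and 334 for 70% vs 55%, an odds ratio of 1.8, 80% power and two-sided 5% alpha. An odds ratio of 1.8 from 55% gives 68.75%. With pooled variance and a 2:1 ratio this needs 145 in the smaller group; 145 × 1.15 = 167 and 2 × 167 = 334, as stated. The percentages 70% and 55% correspond to an odds ratio of (0.70/0.30)/(0.55/0.45) = 1.91 and need 121, or 121/0.85 = 143 after 15% loss. The present point does not depend on that discrepancy; only the 15-point planned difference is used below.

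**2. Who is treated differently.**

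| Screen-positive woman | Cohort One | Cohort Two |
|---|---|---|
| Identified by the provider | Provider's current care | mhGAP care |
| Unidentified, high risk | Referred | Advised to return |
| Unidentified, not high risk | No study action stated | Advised to return |

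The asymmetry lies mainly in the last row. The suicidality criterion is worded differently in the two sections (a score of 3 or more on item 10 in one, ideation or endorsement of the item in the other). The passages must be reconciled before this row can be delimited exactly.

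**3. Which outcomes are exposed.** In both cohorts the EPDS comes after the consultation. Identification at that consultation is settled before any advice can act, so it is protected. Treatment received and 6-month remission come later and are exposed. Primary outcomes gives no time point for identification, so the protection holds only if the index consultation is the time point used.

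**4. Illustrative size.** Assumptions: 55% remission under pre-training care and 70% under mhGAP care (Sample size), with Cohort One at 55%; a share d of Cohort Two identified by providers; a share a of the unidentified acting on the advice and receiving mhGAP care. The document gives neither d nor a. The Discussion says that up to 50% of cases are missed even in well-resourced settings, so d = 0.5 is taken as the central assumption.

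- Points through provider detection = 15 × d
- Points through study advice = 15 × (1 − d) × a

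| d | Provider detection | Advice, a = 0.4 | Advice, a = 0.8 |
|---|---|---|---|
| 0.3 | 4.5 | 15 × 0.7 × 0.4 = 4.2 | 15 × 0.7 × 0.8 = 8.4 |
| 0.5 | 7.5 | 15 × 0.5 × 0.4 = 3.0 | 15 × 0.5 × 0.8 = 6.0 |
| 0.7 | 10.5 | 15 × 0.3 × 0.4 = 1.8 | 15 × 0.3 × 0.8 = 3.6 |

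At d = 0.5 the advice supplies 3.0/10.5 = 29% to 6.0/13.5 = 44% of the observed difference. These are upper values. High-risk women are acted on in both cohorts, so if a share h of the unidentified is high risk, the advice terms shrink towards (1 − h) times the figures shown. Later detection by providers without the advice would shrink them further.

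**5. Effect on power.** With 85% of 167/334 analysed (142/284) and no allowance for clustering, d = 0.5 and no advice gives 62.5% vs 55% and power of about 32%. With full uptake the contrast is 70% vs 55%, with power of about 86%. The advice can therefore bear on whether the trial is positive.

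**The case against.** **The effectiveness question concerns care delivered after training.** Advised women return to trained providers, and the advice alone delivers no mhGAP care. A gain among them is partly a training effect, and psychoeducation is the intervention itself. This stands, and it is why the contrast should be called a mixture and not spurious. It does not show that the gain would occur in routine care without the research EPDS.

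**The design is openly an uncontrolled before-and-after study**, and the Discussion accepts that changes may have other causes. That caveat covers unforeseen outside events. This difference is built into the procedure, has a known direction, and can be traced woman by woman.

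**Wording.** Women are advised, not sent, and the section does not say who advises them. The Cohort One list of high-risk groups need not be exhaustive. Both remarks are fair, and neither removes the asymmetry.

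**Stronger readings that a reader might infer, and that the document does not support:**

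- *Provider identification is itself biased.* The EPDS follows the consultation in both cohorts, and nothing says that identification after the advice is counted.
- *The advice accounts for 6 to 12 of the 15 points.* That is 15 × 0.4 to 15 × 0.8 applied to all of Cohort Two, which requires providers to identify nobody.
- *55% is an untreated rate.* Sample size gives it as the assumed recovery before training, that is, under current care.
- *Replacing advised women's outcomes with Cohort One predictions gives a lower bound.* Being unidentified is a post-training selection, and the replacement would erase benefit from later provider detection, for example through PHQ-2 at subsequent visits in half the clinics.

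**Conclusion.** The concern holds for 6-month remission and for any treatment-received outcome. Both mix provider training with the study's own case-finding, mainly among unidentified women below the high-risk criteria. It does not hold for identification at the index consultation.

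The size cannot be determined from the document. With half of Cohort Two unidentified and 40-80% uptake, the advice adds about 3 to 6 of the planned 15 points. The range is 1.8 to 8.4 points for provider detection between 70% and 30%. These figures rest on the plan's 55% and 70%, on assumed detection and uptake, and on ignoring the high-risk women acted on in both cohorts.

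A positive remission result would support training together with study EPDS advice. It would not by itself show the effect of training in routine care. The two statements of the primary implementation outcome are a separate inconsistency, but it matters here because only the treatment part is exposed to the advice.

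**What to change.** 1. State that the primary implementation outcome is provider identification at the index consultation, before the EPDS result is known. Reconcile Primary outcomes with the Abstract's wording, and report treatment separately by index-identified versus study-advised status. Study status says that the 6-month assessments are complete in both cohorts, so record openly when this choice was made.
2. Flag each Cohort Two woman as index-identified or study-advised. Identification status is already needed to decide who is advised, so the flag follows from the procedure. Report remission by this flag descriptively only, because it is a post-training variable and its groups are selected.
3. Describe the remission contrast as *training plus study EPDS advice*, not as the effect of training in routine care, and add the asymmetry to the limitations.
4. Present any model-based replacement of advised women's outcomes only as a sensitivity analysis under stated assumptions, not as a lower bound.

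The cost is some wording, one derived variable and a narrower effectiveness claim. No change to care is proposed.

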### Interventions

The interventions will be based on treatment specifications in the WHO Mental Health Gap Action Programme Intervention Guide (mhGAP-IG) as adapted for the health system of Nigeria [27]. The mhGAP-IG depression module provides detailed guideline for the management of moderate to severe depression with special consideration for pregnant or breastfeeding women. The mhGAP-IG emphasizes the use of psychosocial interventions for depression in pregnant and breast-feeding women with the lowest effective dose of an antidepressant being used when there is no response to psychosocial treatments. In line with this, interventions for perinatal depression in this study will include psychoeducation, addressing current psychosocial stressors and reactivating social networks.

Psychoeducation will be offered to every woman enrolled into the study as well as to their family members as appropriate. Psychoeducation involves an explanation of the diagnosis to the patient in simple language using local expressions while avoiding the labelling of ‘mental illness/disorder’. The patient is helped to understand that the symptoms being experienced are not as a result of laziness or supernatural forces but an ailment that is common and amenable to treatment. Addressing current psychosocial stressors entails offering the patient an opportunity to talk about current psychosocial problems and, to the extent possible, the health worker addressing pertinent social issues and assisting the patient to solve the problems with the support of available community resources. In reactivating social networks, the patient is encouraged to re-initiate prior social activities that have been neglected on account of the illness.

The health worker is expected to follow up the patient regularly. However, the choice of the number and frequency of the visits will be at the discretion of the attending health care provider. Low dose medications will be indicated for women who do not improve with the psychosocial treatments. Medication will only be given after consultation with the primary care physician.

## Outcome measures

### Primary outcomes

The primary implementation outcome is change in the identification of perinatal depression between the two cohorts by the providers. The primary effectiveness outcome is difference in remission rates from depression at 6 months between the two patient cohorts. Remission is defined as an EPDS score of 5 or less at 6 months post-partum.

#### Secondary effectiveness outcome

The secondary effectiveness outcome will be (1) the difference in the level of disability between the two patient cohorts at 6 months post-partum as assessed with the WHO-DAS [28]; and (2) difference in infant growth and development outcomes between the two cohorts.

#### Secondary implementation outcomes

A range of mixed-methods assessments will be conducted.Assessment of quality of intervention: We will conduct a detailed assessment of fidelity with mhGAP-IG specifications for treating depression by the providers. This will be done by research supervisors sitting in during clinical encounters between PHCW and depressed women. We will use the 18-item Enhancing Assessment of Common Therapeutic factors (ENACT) rating scale [29] to evaluate the extent to which providers are using the skills acquired during the training to provide appropriate psychological assessment and intervention for the women. ENACT is designed to evaluate the delivery of psychological interventions, especially as prescribed in the mhGAP-IG. We will modify it to also include decisions about referral and use of medication. Twenty five consultations will be rated with the tool.Assessment of contextual factors affecting delivery of intervention: Qualitative interviews will be conducted with selected PHCW (N = 20) and women who recover from depression and remain well through the follow-up period (N = 15) and those who fail to make consistent recovery (N = 15) to understand contextual factors that enable/inhibit the delivery of effective treatment using the mhGAP-IG. We will be interested to learn how integrated care of perinatal depression has improved overall health care (for example improved quality of communication with service users, improved service user satisfaction with care), how it has impacted on the functioning of the different components of care, including factors that facilitate or act as barriers to the delivery of intervention at a systems level (for instance information, human resources), as well as issues relating to stigma and discrimination.Process evaluation: we will be conducting process evaluations alongside to enable us to (1) assess the quality of implementation, and (2) identify contextual factors that could affect the scaling up of interventions for perinatal depression. We will target two processes for detailed evaluation- the training of the primary care workers by the trained trainers and the delivery of the interventions for depression using the mhGAP-IG.The training process: We will assess the changes in knowledge and attitude of the trainers following the ToT workshop using pre and post-test questionnaires, knowledge of depression scale [30], and depression attitude questionnaire [31] administered before and after the training sessions. We will evaluate the extent to which trainers demonstrate fidelity to the training procedure when they train the PHCW. Master trainers will sit in at the training workshops delivered by the trained trainers as non-participant observers. During these observations, the master trainers will document their assessment of the training procedure using a semi-structured observation pro forma specifically designed for this purpose. Some of the cascade training sessions will be video-recorded for further training purposes.The Trainees: We will similarly assess the changes in the knowledge and attitude of the trainees who will be at the frontline of delivering the interventions. This will be done using: (1) Pre- and post-test questionnaires, (2) Selected items from the Knowledge of depression scale, (3) Depression attitude questionnaire (4) Satisfaction with training- a semi-structured questionnaire designed to capture: what they liked most about the training, what they had not understood about training topics, what they would do differently as a result of the training, (5) Changes in practice after the training 6) Retention of knowledge and changes in attitude- (at 3, 6, 12 months after training) using Post-test questionnaire, Knowledge of depression scale and the Depression attitude questionnaire.Other process evaluation activities: We will document and link to our Theory of Change Map findings of assumptions/potential barriers and facilitators. We will also track and monitor turnover, availability and transfer of mhGAP-trained staff and supervisors, frequency of supervision sessions, women's attendance for follow-up sessions, and also track any contextual changes in the course of the study.

4. Observational component: Throughout the study period, trained research assistants and field supervisors will pay both scheduled and unscheduled visits to the facilities to document both the visible existing organisational and operational aspects of delivering care for perinatal depression using a pre-designed pro forma. This is essentially to supplement and triangulate the information obtained from key informant interviews and focus group discussions.

5. Effects of COVID-19: Although unexpected, the pandemic might affect the later stages of the recruitment and follow up period. If this happens, we plan to track factors related to COVID-19, for example, in terms of patient flow, ease and regularity of follow up, any increase in domestic violence due to lock down, given its strong association with depression in women.

